### Randomization

Randomization will take place on an individual level. Before providing informed consent, participants are fully informed about the trial’s randomization procedures. Following inclusion, i.e., between T0 and T1, participants will be randomized to one of 6 study arms (3 PrevOP-MMT * 2 PrevOP-PAP conditions, see Fig. 2), using computer-generated random numbers, stratified by gender. Randomization procedures take place outside the study center at the Institute for Clinical Epidemiology and Applied Biometry at Tübingen University Medical Center. PrevOP-PAP study staff are informed about participant allocation to intervention arms via fax by the end of the baseline phase.

### Masking

Regarding study staff conducting the PrevOP-PAP intervention sessions, allocation of participants to intervention or control conditions cannot be masked. Study staff know participants’ allocation at the beginning of the face-to-face computer-assisted intervention session (T1). Moreover, allocation to study condition cannot be masked for participants, as upon inclusion, they are provided a-priori information on the existence of different PrevOP-PAP conditions and randomized allocation to one of them. Analyses of data will be conducted by PrevOP-PAP study staff and will not be masked.

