### Data collection and entry

Data are collected over a 2-year period (i.e., participants remain in the study for 2 years) at 6 measurement points (or periods) in time (T0 to T5) by trained study personnel (see Fig. 3). Inter-measurement intervals range from daily to 6 months, depending on the assessment in question. Data are assessed with self-report questionnaires and objective measures (e.g., accelerometers, body weight). Participants schedule assessment sessions at the study center at Charité – Universitätsmedizin Berlin. During assessment sessions, they are handed a questionnaire booklet, asked to complete it during the session and instructed to turn to study staff with questions (T0, T2, T3, T4, T5; T1 is the main intervention session with additional assessments). At T0, T3, and T5 participants undergo further medical examinations and are handed and instructed to wear accelerometers for eight days. At the end of T0, T3, and T5 periods, i.e., following each one-week accelerometer assessment, participants are additionally asked to complete a brief self-report measure on their daily PA during the past week. Completed study materials and accelerometers are either directly returned to study personnel or mailed to the health psychology lab at Freie Universität Berlin. Data entry will be conducted by trained PrevOP-PAP study personnel. Quality management of data entry will include guidance by a data entry manual, regular plausibility checks, and double entry of portions of the assessed data.

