#### Hypotheses tests

Longitudinal mediation analyses will be conducted using manifest path analyses. PrevOP-PAP-condition will be specified as a dummy-coded independent variable, accelerometer-assessed MVPA as a mediator (in minutes per week), and WOMAC scores as the primary outcome (controlling for respective baseline assessment). Dummy-coded PrevOP-MMT-conditions will be routinely tested as moderators of the association between MVPA (mediator) and WOMAC (primary outcome). If no interactions occur, PrevOP-MMT-conditions are tested as simple-effect covariates and dropped only if they are not related to the mediator or primary outcome. Further covariates are determined by results of the randomization check and bivariate correlations of assumed covariates with primary or secondary outcomes. Significance of all indirect effects will be tested using bootstrapping methods.

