A further strength of the RCT is its fairly long follow-up period of 24 months with a sufficient time span without interventions (12 months) to examine longer-term effects of the PrevOP-PAP on the maintenance of regular PA. Moreover, several repeated assessments allow for testing mediation processes. Again, these benefits come with certain risks, such as a relatively high expected dropout over the two years or increased participant burden due to intense intervention regimens and several repeated assessments. A number of precautions against attrition are realized within the PrevOP trial [65]. For instance, there is an active control group, participants are regularly contacted and reminded of the remaining interventions and assessments, and appointments are scheduled upfront. Many of the assessments and intervention components of both the PrevOP-PAP and PrevOP-MMT are face to face, which may also increase participant commitment.

Furthermore, computer-assisted intervention sessions facilitate standardized delivery of intervention contents, but leave room for individual interaction and tailoring intervention contents and delivery to participants’ needs.

In addition to the strengths and risks reviewed above, this RCT also has a number of limitations. An important limitation is the lack of masking or blinding within the PrevOP-PAP-I. Due to ethical and practical reasons masking is not feasible in this trial. Participants are informed about the possibility to be randomly allocated to intervention or control conditions upon inclusion and study staff are aware of the treatment they deliver. Moreover, although the PAP-I includes a network-creation component and participants are asked about social exchange processes with their sports companions and/or close others, there are no data generated by these other persons. Thus, dyadic or group effects cannot be studied in a fully reciprocal manner in this study [66]. Additionally, except for the accelerometer and assessed medical data, this study largely relies on self-report measures that are subject to recall bias and mere measurement effects as reviewed above.

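### The data analysts are left unmasked, although the reasons given cover only participants and session staff, while model terms are still to be chosen from the data

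*Protocol article*

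**What the plan says.** The Masking section makes three statements.

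- Session staff: "Regarding study staff conducting the PrevOP-PAP intervention sessions, allocation of participants to intervention or control conditions cannot be masked".
- Participants: "allocation to study condition cannot be masked for participants, as upon inclusion, they are provided a-priori information".
- Analysts: "Analyses of data will be conducted by PrevOP-PAP study staff and will not be masked".

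The first two say that masking cannot be done. The third says only that it will not be done, and gives no reason. The Discussion lists the lack of masking as a limitation and adds: "Due to ethical and practical reasons masking is not feasible in this trial". The explanation that follows again names only informed participants and staff who know which treatment they deliver.

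Two other sections show where allocation knowledge and data handling sit. Under Randomization, "Randomization procedures take place outside the study center", at an external biometry institute, and allocations are then faxed to PrevOP-PAP staff. Under Data collection and entry, "Data entry will be conducted by trained PrevOP-PAP study personnel".

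Under Hypotheses tests, parts of the primary model are left to the data: "Further covariates are determined by results of the randomization check and bivariate correlations of assumed covariates with primary or secondary outcomes". The main-trial arms are first tested as moderators. If no interaction appears, "PrevOP-MMT-conditions are tested as simple-effect covariates and dropped only if they are not related to the mediator or primary outcome". The section on drop-out and intention to treat adds predictors of drop-out to the missing-data model according to the differences observed.

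**The concern.** Participants and session staff cannot realistically be masked to a behavioural programme. An analyst can be, because the analysis needs to know which participants share an arm, not which arm received the programme. The article gives up this safeguard without a reason.

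The loss would matter little if every model term were fixed. Here several terms are settled only after the data are seen, by a group that knows the allocation. A borderline decision on a covariate, on a main-trial term or on a drop-out predictor can then be taken with its effect on the arm comparison visible. At stake is whether the primary result can be shown to be independent of those decisions.

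**Working it through.** The plan attaches no figure to this point, so the first two steps compare the text with itself. The third is an illustration on assumed inputs.

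**1. Do the stated reasons reach the analyst?**

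- Participants know that different conditions exist. This does not concern the analyst.
- Session staff know what they deliver. This would concern an analyst only if the same person delivers sessions, which the article does not say. Even then, recoded IDs would break the link to known participants.
- The Discussion calls masking infeasible in general terms but supports this with the same two reasons.

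No stated reason applies to analysis on a coded file.

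**2. Does any open choice need the arm's identity?**

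- Randomization check: compares baseline values between two groups, so labels A and B suffice.
- Covariate screen: uses correlations with outcomes, so no arm label is needed.
- Main-trial terms: depend on their relation to physical activity and WOMAC, so the PrevOP-PAP label is not needed.
- Drop-out predictors: compare continuers with non-continuers, so no arm label is needed.

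All four can be completed on coded labels. The manipulation checks are different: they examine what the programme targets and could reveal the arm.

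**3. Would coding alone be enough?**

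A null simulation (no arm effect, 3,000 runs per row) addresses this.

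- From the document: 240 × (1 − 0.20) = 192 completers, WOMAC stability 0.68, alpha 0.05 (taken as two-sided).
- Assumed: k optional covariates, each correlated 0.2 with the outcome and free to be included or left out, giving 2^k candidate models.
- Outcome: 0.68 × baseline + 0.2 × (sum of covariates) + error.
- Model: outcome regressed on baseline, arm and the chosen covariates.

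| k | Models | Any model significant | Falsely favourable, arms known | Falsely favourable, arms coded, largest absolute effect picked |
|---|---|---|---|---|
| 0 | 1 | 5.2% | 2.8% | 2.8% |
| 3 | 8 | 10.1% | 4.9% | 4.9% |
| 5 | 32 | 16.2% | 7.5% | 7.5% |

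A single model fixed in advance with all covariates gave 4.9% (k = 3) and 4.8% (k = 5). The Monte Carlo standard error near 5% is √(0.05 × 0.95 / 3000) = 0.4 percentage points.

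The last two columns agree. A masked analyst who selects freely produces as many falsely favourable results as an unmasked one. The difference lies in the other direction: the masked analyst also reports false results against the programme, 10.1 − 4.9 = 5.2% for k = 3 and 16.2 − 7.5 = 8.7% for k = 5, which an analyst who knows the arms could pass over. Coding therefore removes steering towards one arm. Only fixing the choices beforehand removes the inflation.

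The simulation tests a direct arm effect on WOMAC, whereas the plan tests a bootstrapped indirect effect. It shows the mechanism and does not estimate this trial's error rate.

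**The case against.** The strongest reply is that the article discloses the lack of masking as a limitation and fixes much of the analysis. Intention to treat, baseline adjustment, bootstrapped indirect effects and the link between missing-data method and analysis method are all set. The main-trial terms follow a stated sequence, and neither that sequence nor the drop-out comparison refers to the PrevOP-PAP effect. A separate analysis plan may list covariates and thresholds. All of this stands and narrows the point. It does not remove it: a separate plan could mask the analysts only by contradicting the article's explicit sentence, and disclosure is not a reason.

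A reader might infer more than the document supports:

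- **That the simulated error rates are the cost of unmasked analysis.** They measure open model choice; coded labels alone left the falsely favourable rate unchanged.
- **That the analysts developed or deliver the programme.** The article says PrevOP-PAP study staff and does not identify the individuals.
- **That accelerometer validity is at the analyst's discretion.** The Physical activity section fixes it at 4 or more days of 10 or more hours.
- **That masking the analyst protects the self-reported WOMAC.** It does nothing about reporting bias in participants who know their arm.
- **That the change costs nothing.** PrevOP-PAP personnel enter the data, and calendars bearing participant codes exist only in the intervention arm, so someone else must hold the key.

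**Conclusion.** The point holds in a limited form. The analysts are left unmasked by explicit statement, the reasons offered do not cover them, and several model terms are chosen from the data by a group that knows the allocation. Coded analysis with choices locked before unmasking would remove this route to bias, and nothing in the document shows it to be infeasible.

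The size of the bias cannot be derived from the document, and no figure should be attached to it. The conclusion assumes that IDs can be recoded so that analysts cannot link them to participants they know, and that intervention-only records can be kept out of the analysis file. It is a cheap improvement, not an error that invalidates the plan.

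**What to change.** Replace the sentence on analysis in the Masking section with a rule along these lines:

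1. The primary analysis is prepared on a file with recoded participant IDs and PrevOP-PAP arms labelled A and B, without activity calendars or session records.
2. The key is held by someone outside the analysis, for example the external randomization institute if it agrees. The article gives it only the randomization, so this role would be new.
3. The covariate set, the handling of main-trial terms, the missing-data model and the primary analysis script are fixed and dated before the labels are released.
4. Manipulation checks that could reveal the arm are run after unmasking.

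Step 3 is as necessary as step 1, because coding alone leaves the inflation from selecting among models.

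The cost is some data-management work, agreement on a keyholder and a short delay before labelled results. Recruitment was still under way when the article was submitted and follow-up lasts 24 months, so the change could still have been made at that stage and reported as a protocol modification, which the article provides for.

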### Brief motivation treatment for all participants

A brief motivational intervention will be delivered to all participants via printed material containing an information leaflet that participants will be asked to read and a brief quiz to test recollection of the information conveyed via the leaflet.

The motivation treatment leaflet contains information on increasing PA for persons with OAK, introduces different intensities of PA and PA guidelines for persons with OAK, and addresses outcome expectancies, risk perceptions, self-efficacy beliefs, and role models related to PA [3, 17, 43]. Below, associated behavior change techniques (BCTs; [13]) are provided in brackets, following the description of text provided in the leaflet. The leaflet is printed in color on a single Din-A 4 page (front and back) that is folded twice and thus includes 6 individual pages. Throughout the leaflet, text passages are interspersed with photos suggesting success in PA, depicting sports utensils, framed summary messages, and illustrations meant to underscore the topic of the respective section. The title page of the folded leaflet informs about the project title and depicts the study logo, the logos of the collaborating institutions, as well as a photograph of a walker’s walking calves and sneaker-clad feet.

The second page starts with a brief basic description of the etiology, risk factors, symptoms, and functional limitations associated with OAK [44] and closes with a statement that evidence indicates that regular joint-friendly activity can help to slow the progression of OAK [3, 44, 45]. This section is interspersed with brief framed calls for PA. On the third page, activity guidelines for persons with OAK are stated, activities of different intensities and types (moderate and vigorous, as well as muscle-force strengthening exercises) are explained and examples of joint-friendly moderate activities and muscle-force strengthening exercises are given (BCTs 1.1, 4.1, 9.1; [3, 13]).

The fourth and fifth pages introduce generic and OAK-specific benefits of daily PA, followed by a list of risks of insufficient activity, and often anticipated negative outcomes of PA. Following this, a brief introduction of the role of negative and positive outcome expectancies for motivation is presented (BCTs 5.1, 5.6; [13]). The final page addresses the participants’ social environment. Participants are asked to reflect what their social network would think of them becoming more active (BCT 3.1; 5.3; [13]) and think about PA role models in their network. This then leads to a brief section on the role of self-efficacy for motivation, asking participants to use self-instruction and exploit former mastery experiences for an increase in PA-specific self-efficacy (BCTs 10.4, 15.3, 15.4, 16.3; [13]).

The *quiz* is delivered in form of a cross-word puzzle. Participants are asked to complete 8 (partially solved) fill-in-the-blanks statements on subject matters introduced by the motivation leaflet and then transfer the filled-in terms to a cross-word puzzle with a pen. The backside of the quiz sheet features the correctly completed cross-word puzzle.

### PrevOP-PAP intervention and -control conditions

The PrevOP-PAP is designed to improve motivation to be physically active and enhance exercise adherence by conveying volitional self-regulation strategies to improve maintenance and prevent relapse to sedentary behavior in persons with OAK.

#### PrevOP-PAP-control condition (PrevOP-PAP-CTRL)

Participants within the PAP-CTRL (*n* = 120) will receive the motivation treatment at T1, but no further psychological interventions. Instead, like the individuals from the PrevOP-PAP-I condition, PAP-CTRL participants receive multiple assessments to monitor changes in primary and secondary outcomes.

#### PrevOP-PAP intervention condition (PrevOP-PAP-I)

Participants (*n* = 120) within the PrevOP-PAP-I will receive a comprehensive intervention program during the first year of study participation (Fig. 3). Motivational interviewing and self-regulation education will take place, which are boostered at regular intervals. The main intervention delivery modes addressing PrevOP-PAP-I components will be computer-assisted face-to-face and phone-based interventions, conducted by trained study staff and paper-pencil materials (PA calendars). The PrevOP-PAP-I is compatible with all PrevOP-MMT conditions in that participants can use self-regulation strategies to maintain all specific PrevOP-MMT-instructed exercise forms (PrevOP-MMT-HIE; PrevOP-MMT-LIE) or self-selected PA (PrevOP-MMT-CTRL). Thus, PrevOP-PAP-I strategies will be parallel across all PrevOP-MMT-conditions.

##### PrevOP-PAP-I computer-assisted face-to-face intervention (week 1 following T0-assessment period; duration about one hour)

PrevOP-PAP-I participants are scheduled to return to the study center at Charité – Universitätsmedizin Berlin following their one-week T0 period. Participants are led to a separate room, take a seat next to the trained study staff and both are guided through the intervention by a computer program seen on the screen of a laptop placed before them. In addition to introductory and feedback sections, the session is divided into four sections focussing on: outcome expectancies, mastery/self-efficacy, goal setting, and planning. Behavior change techniques (BCTs; [13]) used in this part of the intervention are provided in brackets following a brief description of intervention sections described below. The program is presented in a web browser with fill-in options on several consecutive pages. Intervention content-fields are enriched by photos of physically active adults (mid-age to old age), sports utensils, framed summary messages, and depictions meant to illustrate the topic of the respective intervention section.

#### Introduction

The session starts with a reiteration of the project goals (i.e., prevention of OAK progression by means of PA) and the goals of the present intervention session (i.e., develop strategies to implement intentions and overcome barriers). Participants are reminded that PA helps with OAK symptoms, but that regular PA may not be an easy task which is why self-regulation strategies are practiced in this intervention session (BCT 4.1; [13]).

#### Outcome expectancies

Participants calculate their own pros-cons difference of outcomes of regular PA by indicating their agreement with 5 positive (less joint stiffness, good for overall health, enhanced quality of life, stabilize/reduce weight, social contacts) and 5 negative (worsening of symptoms, pain during specific activities, too exhausting, time-consuming, fear of humiliation) outcome expectancy statements on 6-point Likert scales (not at all true – completely true) presented on the computer screen. A score is provided for expected pros and one for expected cons and computed into a benefit expectation difference displayed on the screen. In case of con-scores outweighing pro-scores, participants’ concerns are reviewed and participants are asked to identify activities producing less cons (BCT 9.2; [13]).

#### Mastery/self-efficacy

Working on a PA biography, participants are instructed to recollect types of PA and positive experiences with them throughout their life-span (i.e., childhood/adolescence, early adulthood, middle age; BCT 2.3, 13.1, 13.5; [13]). Activities and experiences are typed into the program by study staff. At the end of this section, an overview of identified PA that were a source of positive experience is provided.

#### Goal setting

This section opens with a reiteration of OAK-specific PA guidelines with explanations for activity types and intensities, and joint-friendly activity examples [3], followed by brief depictions of testimonials by a 61-year old man and a 68-year old woman describing pursuits of their PA goals. Then participants are asked to set and record up to five PA goals (i.e., type of activity, duration) for themselves, they may choose activities they are already performing or set goals for new activities (BCT 1.1; [13]).

#### Planning

Identified PA goals are fed back into the planning section of the intervention. Participants are asked to generate specific action plans for the implementation of their set PA goals. Plans are phrased in an “If/When…, then…” format. Participants are instructed to provide a specific cue situation in the “if/when”-part and describe the planned activity in the “then-”part. An example is provided (“When I come home from work on Wednesdays, then I go aquajogging for 60 minutes”). Then participants are asked to indicate on a 6-point response scale (not at all true to completely true) their agreement with the following statement (plan execution self-efficacy; [46]): “I am sure that I can act as planned in this situation”. Plans are recorded in the computer program. Next, participants are asked to name a start date for the implementation of their plans and copy their plans, as displayed to them on a summary list, into one of the provided activity calendars (see below). Following this, participants are fed back their action plans one-by-one and asked to generate one coping plan for each action plan by (1) thinking about barriers that may keep them from adhering to their action plan and (2) thinking of strategies to manage these barriers (e.g., performing the planned activity at a different time or place and/or performing an alternative activity). Coping plans are also formed in an “If…, then...” format (provided example: “If a spontaneous visit with a friend comes up, then I drive to the friend’s house by bike.”) and all information is recorded. A final summary sheet of all action plans and coping plans is shown (BCT 1.4; [13]).

